### Data management and storage

Data will be manually entered into a database. Data will be stored at the study site following all the secure procedures: demographical and clinical information will be kept locked in dedicated spaces with limited public access. After obtaining informed consent, each participants will be associated with an alphanumeric unique code. Both the database including demographical and clinical information in an anonymous way and the file containing the name of the participants and their codes will be stored on a secure server and they will be protected by passwords. Only authorized research personnel will be access to the database.

### Statistical analyses

An evaluation of type of missing data will be performed in order to detect any missing not-at-random outcome data. A subsequent data-imputation technique (Bayesian imputation) will be applied to obtain complete outcome data. Descriptive statistics will be carried out with parametric and non-parametric tests accordingly to probability data distribution. The analyses of correlation between metacognitive profiles and specific clinical and morphological brain features (i.e. cortical thickness, regional volumes) will be assessed by linear and/or generalized linear models. For longitudinal analyses we will adopt the generalized linear mixed model or generalized estimating equation (GEE) models based on the covariance structure of the data. Lastly, to identify possible predictors of response, we will adopt logistic regression models where clinical and brain markers will be the covariates and the treatment response will be the dichotomous outcome.

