The aim of the present study is twofold. The primary outcome will be the change in emotion dysregulation, measured by the Difficulties in Emotion Regulation Scale – DERS, [36, 37] after 12 months of MIT treatment in subjects with BPD. The secondary outcomes will be the effect of MIT on neurobiological (changes in cerebral patterns of activation in response to emotional visual stimuli during fMRI scans) and other clinical features. Lastly, we will study the correlation between patients’ metacognitive profiles and structural and functional brain imaging features.

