### Sample size

We consider as primary outcome the DERS score and assume quite homogenous population in terms of DERS scores among the recruitment centers. Previous studies reported that the standard deviation (SD) of DERS was 20.7 in females and 18.8 in males [36]. Thus, we assumed a SD of about 20 points. In addition, the correlation between two evaluations (12 months apart) was expected around 0.7 (indicating that about 50% of the variance of the second measurement should be explained by the first measurement). We computed that the SD of DERS changes will be about 15. Our hypothesis is that MIT will decrease DERS more than SCM and, more precisely, a difference between MIT and SCM mean effect larger than 10 points will be considered clinically relevant. To recognize such difference as statistically significant (at bilateral alpha level of 0.05) with an adequate power (0.80), the total number of patients to be recruited should be 60, raised up to 80 (40 MIT + 40 SCM), considering an attrition rate around 20%.

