### Randomization

After baseline assessments, eligible participants will be assigned to treatment arms using randomly generated block randomization scheme within each center. Considering the trade-off between the clinical best practices (e.g. The minimization of waiting list for patients) and rigorous statistical-methodological procedures, block size is fixed equal to 4. With this block size and the two arms (named 0,1), there are 6 different ways -type of blocks Bi- (as result of combination of 4 subjects into 2-element grouping) to allocate the patients: B1 [0011]; B2 [0101]; B3 [0110]; B4 [1010]; B5 [1001]; B6 [1100].

The 80 patients of the project will be randomly assigned to the two arms by a random choice (with replacing) of 20 blocks among the six blocks above defined. For the random choice, the ‘sample’ command of the statistical software R was used (sample (1:6, 20, replace = T)). Random allocation will be done by a statistician. Within 2 weeks, the clinician in charge for clinical evaluation will enrolled the patients and will communicate the experimental arms.

Given the nature of the psychological treatment neither the therapists nor the participants can be blinded for the delivered treatment.

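### The longitudinal model for DERS is left as GLMM or GEE, to be picked from the data's covariance, and is not tied to the 12-month MIT–SCM contrast that sized the trial

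*Protocol article*

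**What the plan says.** The Statistical analyses section first plans an evaluation of the type of missing data and a Bayesian imputation to complete the outcomes. It then lists descriptive tests, linear or generalized linear models relating metacognitive profiles to clinical and brain features, a longitudinal model, and logistic regression for predictors of response. On the longitudinal model it says only "we will adopt the generalized linear mixed model or generalized estimating equation (GEE) models based on the covariance structure of the data". It names no primary contrast and no covariates.

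Other sections bear on that sentence:

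- **Background (aims):** the primary outcome is DERS change "after 12 months of MIT treatment in subjects with BPD". This gives a time point but no comparator.
- **Primary outcome:** change in emotion regulation on the DERS, with neither time point nor comparator.
- **Clinical assessment:** visits at baseline, 6, 12 (end of treatment) and 18 months.
- **Sample size:** the target is between arms: "a difference between MIT and SCM mean effect larger than 10 points will be considered clinically relevant". The inputs are a test "at bilateral alpha level of 0.05", power 0.80, "we assumed a SD of about 20 points", a 12-month correlation of about 0.7 and an SD of change of about 15. The authors also "assume quite homogenous population in terms of DERS scores among the recruitment centers".
- **Randomization:** allocation is made "using randomly generated block randomization scheme within each center", with blocks of 4.

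**The concern.** A rule that picks the model family from the observed covariance leaves the primary p-value open to a decision taken with the data in hand. The criterion is also the wrong one. A mixed model and a GEE both accommodate correlated repeated measures, and inspecting that correlation does not tell the analyst which to use. They differ in how they treat missing outcomes and in how their standard errors behave in small samples. Both matter in a trial of 80 patients that expects about 20% attrition.

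Three post-baseline visits add a second freedom. A longitudinal model can yield an arm difference at 6, 12 or 18 months, an average over visits, or a difference in slopes. The sample size concerns one of these. The analysis section does not say which is primary, and the aims sentence taken alone does not mention the comparator.

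The planning also rests on the SD of raw change, although the assumed correlation means that baseline DERS carries further usable information. Naming baseline as a covariate would secure that precision, and naming centre would match the analysis to the stratified allocation.

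**Working it through.** **1. Does the sentence govern the primary outcome?** It is not labelled as the primary analysis. Of the methods listed, however, only the longitudinal model suits a continuous score measured at several visits in two arms.

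**2. Does covariance separate the two families?** No. For a continuous score with an identity link, both target the same mean difference between arms. What differs is:

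- *Missing outcomes.* Unweighted GEE on observed data needs data missing completely at random. A likelihood-based mixed model needs only missing at random.
- *Small samples.* Take a simple two-arm comparison with 32 per arm, an uncorrected sandwich variance and a normal critical value. The true type I error is 2 × P(T62 > 1.96 × √(31/32)) = 0.058, against a nominal 0.05.

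**3. The plan's own figure.** Var(change) = 2 × 20² × (1 − 0.7) = 240, so the SD is 15.49 (the article says about 15). With n per arm = 2 × (1.96 + 0.84)² × SD² / 10²:

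- SD 15: 36 per arm, total 72.
- SD 15.49: 38 per arm, total 76.

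The stated 60 is not reproduced with a two-sided test. A one-sided 0.05 test with SD 15.49 gives 30 per arm, total 60. This is a separate defect, but it sets the starting power below.

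**4. What baseline adjustment is worth.** The baseline-adjusted variance is 20² × (1 − 0.7²) = 204, SD 14.28. The ratio to change scores is 204/240 = 0.85, or (1 + r)/2 in general. That equals about 1/0.85 − 1 = 18% more patients.

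Power for a 10-point difference, two-sided 0.05, by noncentral t (change score with 2n − 2 df, adjusted with 2n − 4 df). The 64 is 80 less 20%; the 60 is the article's own target.

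| r | Evaluable | Change score | Baseline-adjusted |
|---|---|---|---|
| 0.7 | 64 | 0.72 | 0.79 |
| 0.7 | 60 | 0.69 | 0.76 |
| 0.6 | 64 | 0.60 | 0.69 |
| 0.6 | 60 | 0.57 | 0.66 |
| 0.8 | 64 | 0.88 | 0.91 |

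At r = 0.7 and 64 evaluable, the difference detectable with 80% power falls from 11.0 to 10.2 points. The share of the shortfall from 0.80 that is recovered at r = 0.7 is (0.787 − 0.720)/(0.800 − 0.720) = 84% at 64, and 63% at 60 by the same formula. At r = 0.6 it is 41% to 47%.

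**5. Centre.** The documents give no between-centre variance, so this gain cannot be computed. As an assumption only, if centre explained 0%, 2%, 5% or 10% of the residual variance at r = 0.7, power with 60 evaluable (normal approximation) would be 0.774, 0.782, 0.794 or 0.815.

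**The case against.** The strongest reply is that a journal article condenses the full plan. Covariates, contrast coding, covariance structure and degrees of freedom usually sit in the statistical analysis plan, which is not shown. That stands, and it rules out several stronger readings that a reader might infer:

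- *That centre is ignored or baseline left out.* The article says neither. The homogeneity statement is a planning assumption in the sample-size section, not an analysis rule. If it were true, omitting centre would cost almost nothing.
- *That the analysis will be a raw change-score test.* Change scores are the planning basis only. A longitudinal model that conditions on baseline, or constrains baseline means to be equal across arms, would already have about the adjusted precision.
- *That GEE would be invalid because it needs data missing completely at random.* The article plans imputation first, and GEE on properly imputed data does not need that assumption.
- *That the sandwich variance makes GEE unusable.* An error rate near 5.8% is modest, and a standard correction removes it.
- *That the primary test is a pre–post test within MIT.* The Abstract, the Sample size section and the Discussion all frame the comparison as MIT against SCM. The aims sentence is loose wording.

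What the reply does not reach is the rule that is written down. Leaving detail to another document does not mend a stated selection criterion that is data-dependent and does not discriminate between the options. The longitudinal sentence also has no link to the 12-month contrast.

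**Conclusion.** The point holds in limited form. The article states a data-dependent choice between two model families for the only listed method that fits the primary outcome, and does not tie that model to the 12-month MIT–SCM difference. The documents do not allow an estimate of how far this freedom could move the p-value.

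The measurable benefit of the fix is 15% less variance than an unadjusted change-score contrast, worth about 7 percentage points of power at 60 to 64 evaluable patients. It rests on SD 20 and r = 0.7. With r = 0.6 the gain in points is larger, but power stays below 0.70.

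It would be tempting to conclude that the quoted sentence causes the power shortfall, or that adjustment repairs it. Neither follows. The shortfall comes from 60 being stated where the two-sided inputs need 72 to 76. With adjustment, 60 evaluable still give only 0.76, and 80% power needs 66 (normal approximation) or 68 (t).

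**What to change.** Name one primary analysis, dated before anyone sees outcomes by arm:

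- A linear mixed model for DERS total at 6, 12 and 18 months, in all randomised patients as allocated.
- Fixed effects: arm, visit, arm-by-visit, baseline DERS, baseline-by-visit, and centre as the randomisation stratum.
- Unstructured within-patient covariance, REML, and small-sample degrees of freedom such as Kenward-Roger.
- Primary estimate: the MIT minus SCM difference at 12 months. The 6- and 18-month differences are secondary.
- GEE, if kept, as a sensitivity analysis with a small-sample variance correction.

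State how the planned imputation fits in, because a patient with no post-baseline DERS adds nothing to this likelihood. Reword the aims sentence in Background as the between-arm difference at 12 months, so that it agrees with the Sample size section.

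If the unseen analysis plan already fixes such a model, it is enough to replace the either-or sentence with a reference to it. The cost is wording only: baseline DERS and centre are already recorded. The sample-size calculation needs its own correction.

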**Methods:**

The study design is a randomized parallel controlled clinical trial and will include 80 BPD outpatients, aged 18–45 enrolled at 2 recruitment centers. Primary outcome will be the clinical change in emotion regulation capacities assessed with the Difficulties in Emotion Regulation Scale (DERS). We will also investigated the effect of psychotherapy on metacognitive abilities and several clinical features such as BPD symptomatology, general psychopathology, depression, personal functioning, and trait dimensions (anger, impulsivity, alexithymia). We will evaluate changes in brain connectivity patterns and during the view of emotional pictures. A multidimensional assessment will be performed at the baseline, at 6, 12, 18 months. We will obtain structural and functional Magnetic Resonance Images (MRIs) in MIT-Treated BPD (*N* = 30) and SCM-treated BPD (*N* = 30) at baseline and after treatment, as well as in a group of 30 healthy and unrelated volunteers that will be scanned once for comparison.

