### Primary outcome

The primary outcome measure will be changes in emotion regulation, measured by the Difficulties in Emotion Regulation Scale (DERS) [36, 37]. This scale is a 36-item self-report questionnaire comprising a total score and six dimensions: (1) Non-acceptance of emotional responses (6 items); (2) Difficulties engaging in goal-directed behavior (5 items); (3) Impulse control difficulties (6 items); (4) Lack of emotional awareness (6 items); (5) Limited access to emotion regulation strategies (8 items); (6) Lack of emotional clarity (5 items). The scale showed good psychometric properties, in terms of internal consistency (Cronbach’s alpha between 0.80 and 0.93), construct and predictive validity and adequate test-retest reliability.

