### Neuroimaging analyses

Neuroimaging analyses will aim to 1. assess the structural and functional correlates of BPD, 2. identify biological markers as possible predictors of treatment response, and 3. assess the variations after psychotherapy in cortical and subcortical functional activation in response to a standardized emotional material [63] (Lang et al. 2007) along with structural and functional connectivity. Structural measures will be assessed on MRI using both whole brain cortical thickness analyisis and Region of interest (ROI) analysis of the key subregions involved in emotion regulation (e.g, amygdala). Functional measures will be assessed on task fMRI through a voxel-wise and ROI-Analyses analysis of the fluctuations in the BOLD signal. Structural connectivity analysis will include the assessment of fractional anisotropy, mean, axial and radial diffusivity in the major white matter tracts. The analysis will be carried out both with voxel-wise analysis and ROI approach restricted to the tracts involved in emotion (e.g., limbic tracts).

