## Discussion

The relevance of the project is twofold. First, the population included in the project represents a clinical priority of mental health system for several reasons (high suicidal risk, high direct and indirect costs, long-term impairment and social dysfunctioning), moreover in Italy there is a paucity of intervention specifically oriented to this clinical group.

Secondly, our project’s contribution will be to test the effectiveness of a psychotherapeutic approach and to identify the clinical and neurobiological factors associated with response to the treatment. The inclusion of a multidisciplinary study protocol will allow to study BPD considering different features that can affect the treatment response and their reciprocal relationships.

The RCT CLIMAMITHE will contribute to deepen this topic, studying in particular the change in emotion dysregulation comparing the two treatments and the relation between these and changes in neurobiological aspects. The rationale to include emotional dysregulation as primary outcome is manifold. From a clinical point of view, emotional dysregulation is one of the core dimensions of BPD and the relationship between emotion regulation capacities and metacognitive abilities has not been yet clearly addressed. In the definition proposed by Gratz and Roemer [36], emotion regulation includes also metacognitive aspects (awareness and understanding of emotions, the ability to control impulsive behaviors and to behave flexibly in accordance with desired goals when experiencing negative emotions). We will investigated the relationship between emotion regulation, metacognitive abilities and other BPD features. From a methodological point of view, DERS has demonstrated good psychometric properties, in terms of internal consistency, test-retest reliability and validity [36, 37]. Lastly, DERS has been previously used to measure clinical and neurobiological change after DBT [27].

The use of the same behavioral task during fMRI used in other study will let the results to be comparable and this could diminish the variabilities of their interpretation. Moreover, the expected number of patients to be included could overcome the limitations of other studies with a small sample.

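### Predictors of response are sought on a yes/no outcome, which discards information, and with no arm term named a marker so found is prognostic, not treatment-specific

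*Protocol article*

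**What the plan says.** The Statistical analyses section gives the predictor analysis one sentence. Its purpose is "to identify possible predictors of response". The method, covariates and outcome are fixed by "we will adopt logistic regression models where clinical and brain markers will be the covariates and the treatment response will be the dichotomous outcome". No cut-off for response is given, and the article does not say from which scale response is derived. Neither treatment arm nor an arm-by-marker term is named there or under Neuroimaging analyses.

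The aim returns in two other places. Neuroimaging analyses lists, as one of three aims, to "identify biological markers as possible predictors of treatment response". The Discussion counts it as part of the project's contribution "to identify the clinical and neurobiological factors associated with response to the treatment".

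The primary measure is DERS, described under Primary outcome: "This scale is a 36-item self-report questionnaire comprising a total score and six dimensions". The Sample size section treats change in DERS as continuous, with an SD of about 15. According to the Abstract, patients are scanned in two groups of 30, one per arm, "at baseline and after treatment, as well as in a group of 30 healthy and unrelated volunteers". Brain markers are therefore planned for 60 patients, and clinical markers for up to 80. Both arms receive an active treatment (Interventions).

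**The concern.** Two features of the stated model bear on what it can show.

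First, a numerical score measured on every patient is reduced to yes/no before markers are related to it, and no reason is given. This costs power in a group of 60, where there is little to spare.

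Second, the trial has two active arms. A model with markers alone asks who improves under whichever treatment they received. It does not ask whether a marker predicts benefit from MIT over SCM, and it does not use the randomised comparator. A reader of the results could take a general prognostic marker for a marker of response to MIT. A marker that helps in one arm and harms in the other would tend to cancel out and be missed.

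**Working it through.** The article gives no power or sample-size figure for the predictor analysis, so there is none to reproduce.

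**Inputs from the article.** Scanned patients: 30 + 30 = 60 (Abstract); recruited patients: 80. SD of DERS change: about 15; difference between arms: 10 points; two-sided alpha: 0.05 (Sample size).

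**Assumed inputs, not in the article.** Response is a cut of normally distributed DERS change. The responder share is 50% or 30%. The correlation of marker with change is 0.35 in both arms, or 0.5 in one arm and 0 in the other, or +0.35 and −0.35.

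**Step 1: information kept by a yes/no cut.** For a normal outcome cut so that a share p respond, the efficiency relative to the continuous outcome is φ(z_p)² / [p(1 − p)].

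- p = 0.5: 0.3989² / 0.25 = 0.637; 60 × 0.637 ≈ 38 patients.
- p = 0.3: 0.3477² / 0.21 = 0.576; 60 × 0.576 ≈ 35 patients.
- p = 0.2: 0.2800² / 0.16 = 0.490; 60 × 0.490 ≈ 29 patients.

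The 50% cut is the most favourable case.

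**Step 2: power by direct approximation, r = 0.35.** Power ≈ Φ(atanh(r)·√(n − 3) − 1.96), with atanh(0.35) = 0.3654.

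- Continuous, n = 60: 0.3654 × √57 − 1.96 = 0.799, power 0.79.
- 50% cut, effective n = 38: 0.3654 × √35 − 1.96 = 0.202, power 0.58.

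**Step 3: power by simulation.** There were 4000 runs per cell, with change SD 15 and an arm difference of 10. Each cell gives the share of trials with p < 0.05 at N = 60, for 50% / 30% responders. The share sets the cut; the linear models do not use it, so their paired values differ only by simulation error.

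| True marker effect (MIT / SCM) | Logistic, marker only | Linear, marker only | Linear, marker + arm | Logistic, arm-by-marker | Linear, arm-by-marker |
|---|---|---|---|---|---|
| 0.35 / 0.35 | 0.58 / 0.53 | 0.76 / 0.75 | 0.81 / 0.79 | 0.06 / 0.07 | 0.04 / 0.05 |
| 0.5 / 0 | 0.34 / 0.39 | 0.46 / 0.45 | 0.50 / 0.49 | 0.39 / 0.33 | 0.52 / 0.49 |
| +0.35 / −0.35 | 0.05 / 0.07 | 0.07 / 0.06 | 0.06 / 0.06 | 0.60 / 0.53 | 0.76 / 0.77 |
| 0 / 0 | 0.05 / 0.05 | 0.05 / 0.05 | 0.06 / 0.05 | 0.06 / 0.07 | 0.05 / 0.05 |

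A separate simulation of 1500 runs with a median split at n = 60 gave 0.81 for the continuous outcome and 0.59 after the split. At N = 80, which is relevant for clinical markers, the first row becomes 0.69 / 0.63 for logistic with marker only and 0.90 / 0.90 for linear with marker and arm.

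**Step 4: reading the table.** The first row shows the loss from dichotomising, about 20 points of power. The third row shows what a model without arm-by-marker cannot see: the two effects average to zero, so detection stays near the 5% error rate, whereas the linear interaction test finds the marker in 76–77% of trials. The second row shows the limit of the remedy: about 0.5 for a strong effect confined to one arm.

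The simulated models contain neither baseline DERS nor centre. With the article's SD of 20 and correlation of 0.7, adjusting for baseline leaves a residual SD of 20 × √(1 − 0.49) = 14.28, against 20 × √(2 × 0.3) = 15.49 for change. On these figures, that adjustment should not lower power for a marker unrelated to baseline.

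**The case against.** The strongest reply is that one sentence in a condensed article is not a model formula. It does not say that the arms are pooled, that arm is left out, or that models will not be fitted by arm, and such detail commonly sits in an analysis plan. This stands. A reader might infer that the plan excludes an interaction; the article only fails to name one.

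The aim is also worded modestly. No section promises markers that favour MIT over SCM, and the aims at the end of the Background do not list response prediction. If general predictors are meant, the model answers that question. This stands too. A reader might call it a false positive when the model flags a marker that is prognostic in both arms. It is not: the marker does predict outcome, and the main-effect and interaction tests address different hypotheses.

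Two further inferences lack support. One is that the model is overfitted. The article lists many possible markers but does not say how many enter one model, and it gives no number of responders. The other is that fewer than 60 scanned patients should be assumed. The 60 are described as scanned before and after treatment and match the number before the attrition allowance, so deducting attrition again may count it twice.

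A responder analysis is also common and easy to read, and the article plans continuous models elsewhere: linear or generalised linear models for metacognitive profiles against brain features, and mixed or GEE models for longitudinal data. These do not change the predictor analysis itself, whose dichotomous outcome is written text.

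**Conclusion.** The concern holds in limited form. The firm part is the outcome: a dichotomous response is stated while the main measure is numerical. If response comes from DERS, at most about 64% of the information is kept, and for a correlation of 0.35 at n = 60 power falls from roughly 0.75–0.81 to 0.53–0.59. These figures rest on an approximately normal outcome and on the assumed responder shares and correlation; the article gives neither a cut-off nor a source scale for response.

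The part on treatment arm is conditional. If the model is fitted as written, a detected marker is prognostic under either active treatment, and a marker with opposite effects by arm would be found in only about 5–7% of trials. The article does not rule out an interaction.

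Severity is minor. The analysis is secondary, and the primary comparison of MIT with SCM does not depend on it.

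**What to change.** Make the main predictor analysis a linear model of 12-month DERS on baseline DERS, centre, arm and marker. Add arm-by-marker as the exploratory test of treatment-specific prediction. Label marker main effects as prognostic, and align the wording of the aim under Neuroimaging analyses and in the Discussion. Keep any responder cut-off for description.

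This needs no new data, patients or visits, and it uses the randomised comparator already in the trial. The cost is a change of wording and a more modest claim: interaction power is about 0.5 at N = 60 (0.62–0.63 at N = 80) even for a correlation of 0.5 in one arm and 0 in the other. The interaction results must therefore be called exploratory, and a non-significant interaction must not be read as evidence that a marker works equally in both arms.
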